**Fig. 2 Fig2:**
[figure not shown]
Example clinical target volumes for whole-breast irradiation (WBI) only, high-tangent field irradiation, and axillary and supraclavicular lymph node irradiation. High-tangent field or larger was permitted for postoperative radiotherapy after breast-conserving surgery in the control group (WBI and regional nodal irradiation)

**Fig. 3 Fig3:**
[figure not shown]
Example clinical target volumes for post-mastectomy radiotherapy. No post-mastectomy radiotherapy is permitted in the experimental group. Chest wall irradiation with or without regional lymph node irradiation is allowed in the control group

Regular follow-up visits will be scheduled (at 6 months and 12 months, and once per year thereafter) for 7 years after the day of randomization. Performance status, disease status, survival, and adverse events will be recorded at every follow-up visit.

### Safety monitoring

Adverse events to be recorded include radiation dermatitis, radiation pneumonitis, major reconstruction surgery complications, lymphedema, contralateral ductal carcinoma in situ or invasive breast cancer, major coronary events, ipsilateral rib fracture, and others. Radiation dermatitis and pneumonitis will be evaluated based on the Common Terminology Criteria for Adverse Events (CTCAE) version 5. Major reconstruction surgery complications are defined as unplanned rehospitalization, reoperation for intervention, implant removal due to infection, and autologous flap failure. Lymphedema will be recorded when the participant complains of lymphedema symptoms or additional symptomatic treatment is required. An adverse event will be recorded when ductal carcinoma in situ or invasive cancer in the contralateral breast is histologically diagnosed. Major coronary events include myocardial infarction, ischemic heart failure, unstable angina, and sudden death. Ipsilateral rib fracture revealed by a radiographic or nuclear medical scan will be reported regardless of symptoms. Other adverse events may be recorded and graded according to CTCAE version 5. Severe adverse events should be reported to the institutional review board within 7 working days. An institutional investigator should report all severe adverse events to the primary investigator. A severe adverse events report will be sent to the institutional review board of each participating center.

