### Screening and randomization

Participants will be screened at a radiation oncology department after surgery. After obtaining written informed consent, inclusion and exclusion criteria will be applied based on clinical records, pathologic reports for surgical specimens, and additional history data. Participants who meet the criteria will be enrolled and randomized to the control and experimental groups in a 1:1 ratio. Randomization will be performed by an authorized investigator using a web-based system. The randomization system was devised by the Medical Research Collaborating Center (MRCC) of Seoul National University Hospital and is operated separately from other clinical investigators. Amendment of the randomization process is strictly forbidden by the MRCC. The stratified block randomization method will be used to prepare a randomization table. The stratification factors include surgery type (BCS vs. mastectomy) and histologic subtype (triple-negative vs. non–triple-negative breast cancer). The investigators will submit the screening number, participating institution, date of informed consent, and birthday of the participant to the randomization system to prevent duplicate enrollment. The participants and investigators are not blinded to the randomization results, and the participant may be informed of the precise details and field settings of the radiotherapy. After group allocation is confirmed, the written consent form will be printed and stored with the clinical trial documents.

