### Endpoint and statistics

The primary endpoint of this trial is 7-year DFS. The secondary endpoints are locoregional recurrence-free survival (LRFS), distant metastasis-free survival (DMFS), and overall survival (OS). A DFS event is defined as breast cancer recurrence or death. An LRFS event is defined as recurrence in a locoregional area, including the ipsilateral breast/chest wall, axilla, IMN, and SCL area, or breast cancer death. A DMFS event is defined as distant metastasis or breast cancer death. For OS, an event is defined as patient death from any cause. These endpoints will be measured from the date of randomization.

Categorical variables will be compared between the control and experimental groups using the chi-square test, and continuous variables using Student’s *t*-test. DFS, LRFS, DMFS, and OS rates will be calculated by Kaplan–Meier analysis and compared using the log-rank test. The Cox proportional hazards model will be used to evaluate the impact of covariates on clinical endpoints. The threshold for statistical significance is *P* < 0.05. No interim analysis is planned for this trial.

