This protocol establishes a minimum number of dissected lymph nodes as an additional requirement for patients receiving mastectomy, due to concerns about the risk of locoregional recurrence after insufficient axillary dissection with complete PORT omission. Conventionally, the total number of surgically removed lymph nodes is thought to be associated with breast cancer prognosis [30]. However, this concept has been challenged by studies on the de-escalation of axillary dissection [27, 28]. Nevertheless, researchers remain cautious with respect to omitting both axillary dissection and PORT in cases of node-positive breast cancer. Notably, in ongoing trials examining the de-escalation of axillary surgery, further axillary dissection is being replaced with radiotherapy [29, 31].

We expect a lower prevalence of lymphedema to emerge as a benefit of decreasing the radiation field size and indications for PORT. Lymphedema is a major form of toxicity associated with breast cancer treatment. A recent large Korean retrospective study reported a 3-year lymphedema rate of approximately 10% [32], although the incidence may vary among diagnostic methods [33]. Lymphedema significantly affects the quality of life of breast cancer survivors, both physically and psychosocially [34]. Many studies have linked lymphedema risk with surgical factors such as the number of removed lymph nodes [35]. However, several reports have indicated that wider RNI is also associated with a higher incidence of lymphedema [32, 36, 37]. As an additional objective, this trial will assess whether PORT de-escalation impacts the incidence of lymphedema in patients with pN1 breast cancer. Toxicity and oncologic safety data from this trial are expected to greatly influence clinical decision-making.

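### Lymphedema, the one toxicity named as an expected benefit, is recorded only on complaint or need for treatment in an unblinded trial, so unequal reporting could create or inflate a difference

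*Protocol article*

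**What the plan says.** The Safety monitoring section of the protocol article fixes the rule for this event: "Lymphedema will be recorded when the participant complains of lymphedema symptoms or additional symptomatic treatment is required". It gives no grade, measurement or threshold. The same section is firmer on other events: dermatitis and pneumonitis are assessed with CTCAE version 5, contralateral cancer needs histology, and a rib fracture seen on imaging counts whether or not there are symptoms.

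Screening and randomization states: "The participants and investigators are not blinded to the randomization results". It adds that participants may be told the details of their radiotherapy fields.

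The Discussion says what is hoped for: "We expect a lower prevalence of lymphedema to emerge as a benefit of decreasing the radiation field size and indications for PORT". It then sets the comparison as a task: "As an additional objective, this trial will assess whether PORT de-escalation impacts the incidence of lymphedema in patients with pN1 breast cancer". It cites a 3-year lymphedema rate of about 10% from a retrospective study and concedes that incidence can differ with the method of diagnosis.

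Endpoint and statistics lists locoregional recurrence-free, distant metastasis-free and overall survival as secondary endpoints; lymphedema is not among them. Under Interventions and follow-up, adverse events are recorded at visits at 6 and 12 months and then yearly, on the same schedule in both arms.

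**The concern.** A non-inferiority trial of less treatment persuades by pairing acceptable efficacy with a gain elsewhere. Lower toxicity is part of this trial's stated aim, and lymphedema is the only specific toxicity named as an expected gain. Yet it has the softest recording rule among the events for which the article gives a criterion.

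A case enters the data only if the participant raises symptoms or symptomatic treatment is judged necessary. Both steps can be influenced by knowing the allocation. Someone who knows that her axilla was irradiated may be readier to mention arm symptoms, and a clinician may be readier to ask or to treat. Contact during treatment also differs. Control-arm mastectomy patients attend for 13–17 or 23–28 fractions, while experimental-arm mastectomy patients receive no irradiation. These influences would tend to favour de-escalation. The documents do not show that they will occur; the stated rule does nothing to prevent them.

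At stake is the credibility of the lymphedema comparison.

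**Working it through.** The protocol gives no design figure for lymphedema, so there is none to reproduce. The check asks how often unequal reporting alone would produce a significant difference.

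**Inputs from the protocol**
- Randomized per arm: 525 / 0.95 = 552.6, rounded up to 553; 2 × 553 = 1106, as stated in Sample size calculation.
- Lymphedema rate: 10%, the 3-year figure cited in the Discussion, used here as the true rate in both arms.
- Significance: P < 0.05, with a chi-square test for categorical variables (Endpoint and statistics). Taken as two-sided, this leaves 2.5% in the direction of de-escalation when there is no true difference and no reporting bias.

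**Assumptions, not in the protocol**
- Share of true cases recorded: 90% in control; 80%, 70% or 60% in the experimental arm.
- All 553 per arm contribute to the comparison.
- A true rate of 20%, as a second scenario.

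**Formulas**

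Observed rate = true rate × share recorded. Hence the observed rate ratio is the true rate ratio multiplied by the reporting ratio, and a genuine benefit is inflated by the same factor that would create a spurious one.

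P(significant, favouring de-escalation) = Φ( (pC − pE) / √{[pC(1 − pC) + pE(1 − pE)] / 553} − 1.96 )

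**True rate 10% in both arms**

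| Share recorded, control vs experimental | Observed rates | Reporting ratio | Standard error | Difference / SE | P(false significant) |
|---|---|---|---|---|---|
| 90% vs 80% | 9.0% vs 8.0% | 0.89 | √(0.1555/553) = 0.0168 | 0.60 | about 9% |
| 90% vs 70% | 9.0% vs 7.0% | 0.78 | √(0.1470/553) = 0.0163 | 1.23 | about 23% |
| 90% vs 60% | 9.0% vs 6.0% | 0.67 | √(0.1383/553) = 0.0158 | 1.90 | about 47% |

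**True rate 20% in both arms.** The same three gaps give observed rates of 18% vs 16%, 14% and 12%, and false significant results in about 14%, 44% and 80% of trials.

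**How large a gap is needed?** With a true rate of 10% and every control-arm case recorded, a 50% chance of a false result needs a reporting ratio of about 0.67, and an 80% chance needs about 0.55. At this rate a modest gap raises the error above its nominal level, but only a large one makes a false result likely.

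**The case against.** The strongest reply is that this is a non-endpoint outcome in a trial whose primary question is disease-free survival, and that the reporting shares above are invented. Need for treatment is a second trigger besides complaint, and the scheduled follow-up visits are the same in both arms. The 10% is a single retrospective figure that the protocol itself says depends on method. Lower time and medical costs are also named as gains (Background), so lymphedema is not the whole benefit case. A CTCAE grade given by an unblinded investigator can also be swayed by allocation.

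Most of this stands, and it limits the size of the point. It does not remove it. The rule is stated in the article, not left to a fuller document. It governs a comparison that the article says the trial will make. Equal visit dates do not equalize what is volunteered or asked at them, and the decision to treat is also made knowing the allocation.

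Two stronger readings may tempt a reader, and the documents support neither.
- **Visits starting at month 6 mean that acute dermatitis and pneumonitis are lost, which manufactures a toxicity gain.** The article says adverse events are recorded at every visit. It does not say that earlier events go unrecorded, and severe events have their own reporting route. Any loss would fall mainly on the arm given more radiotherapy and would hide a gain.
- **Lymphedema present before radiotherapy favours de-escalation.** Randomization, stratified by surgery type, balances it on average. Counting it blurs the incidence figure without favouring an arm.

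**Conclusion.** The point holds for the lymphedema comparison. Following the plan exactly, a difference in favour of de-escalation could arise from, or be enlarged by, unequal reporting or asking. Under the assumed reporting shares, with an equal true rate of 10% and 553 per arm, the chance of a false significant result in that direction is about 9%, 23% or 47%, against a nominal 2.5%. These are illustrations of sensitivity, not estimates of the bias to expect.

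A reader might infer that the whole toxicity comparison is unreliable. The text does not support that: contralateral cancer and rib fracture have objective criteria, and dermatitis and pneumonitis are graded. The disease-free survival conclusion is untouched. Leaving lymphedema off the list of secondary endpoints is not an error in itself, since the Discussion labels it an additional objective.

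**What to change.** In Safety monitoring, replace the complaint-triggered rule with a CTCAE version 5 lymphedema grade, including grade 0, entered for every participant at randomization and at each scheduled visit in both arms. Keep complaint or symptomatic treatment as a separate item. Compare new or worsened lymphedema between arms.

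The scale is already used in the protocol and the visits already exist, so the cost is one form item and slightly more data entry. Recruitment began in July 2022, so participants enrolled before the change may lack a grade at randomization. That gap cannot be filled later, which is a reason to act early.

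The change makes the asking uniform; it does not blind the grader or the participant. The remaining bias should be acknowledged when the result is interpreted. A measured definition, or an assessor unaware of allocation, would reduce it further at a higher cost.

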### Data management

The principal investigator has full responsibility for the management of clinical trial data. Investigators will complete case report forms using a web-based system (iCReaT version 2) provided by the Korean National Institute of Health. Data monitoring will be performed by a clinical research organization (Promedis Inc., Seoul, Republic of Korea) and the clinical research coordinator of each participating center. Documents generated from this trial will be stored at each participating center until 10 years after trial completion, with approval from the institutional review board, after which personal information will be discarded.

### Endpoint and statistics

The primary endpoint of this trial is 7-year DFS. The secondary endpoints are locoregional recurrence-free survival (LRFS), distant metastasis-free survival (DMFS), and overall survival (OS). A DFS event is defined as breast cancer recurrence or death. An LRFS event is defined as recurrence in a locoregional area, including the ipsilateral breast/chest wall, axilla, IMN, and SCL area, or breast cancer death. A DMFS event is defined as distant metastasis or breast cancer death. For OS, an event is defined as patient death from any cause. These endpoints will be measured from the date of randomization.

Categorical variables will be compared between the control and experimental groups using the chi-square test, and continuous variables using Student’s *t*-test. DFS, LRFS, DMFS, and OS rates will be calculated by Kaplan–Meier analysis and compared using the log-rank test. The Cox proportional hazards model will be used to evaluate the impact of covariates on clinical endpoints. The threshold for statistical significance is *P* < 0.05. No interim analysis is planned for this trial.

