**Methods:**

The PORT-N1 trial is a multicenter, randomized, phase 3 clinical trial for patients with pN1 breast cancer that compares the outcomes of control [whole-breast irradiation (WBI) and RNI/PMRT] and experimental (WBI alone/no PMRT) groups. PORT-N1 aims to demonstrate non-inferiority of the experimental group by comparing 7-year disease-free survival rates with the control group. Female breast cancer patients with pT1-3 N1 status after BCS or mastectomy are eligible. Participants will be randomly assigned to the two groups in a 1:1 ratio. Randomization will be stratified by surgery type (BCS vs. mastectomy) and histologic subtype (triple-negative vs. non-triple-negative). In patients who receive mastectomy, dissection of ≥5 nodes is required when there is one positive node, and axillary lymph node dissection when there are two or three positive nodes. Patients receiving neoadjuvant chemotherapy are not eligible. RNI includes a “high-tangent” or wider irradiation field. This study will aim to recruit 1106 patients.

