## Methods and design

### Study design

PORT-N1 is a prospective multicenter randomized controlled non-inferiority trial. The study design is illustrated in Fig. 1. Twenty-one academic centers in South Korea are participating in this trial. Participants with 1–3 positive lymph nodes (found during axillary surgery), who did not receive neoadjuvant systemic therapy and underwent BCS or mastectomy, were randomized in a 1:1 ratio to the control and experimental groups. Participants allocated to the control group who underwent BCS will undergo whole-breast irradiation (WBI) with RNI, while those who underwent mastectomy will undergo PMRT. Participants allocated to the experimental group will undergo WBI only if they underwent BCS. PMRT will not be performed in experimental group participants who underwent mastectomy. This trial is anticipated to run for 11 years, with a 4-year recruitment phase and 7-year follow-up. The first participant was recruited on July 19, 2022. Participant registration is expected to be completed in December 2026, and the final results will be available after 2033. This protocol was approved by the KROG and designated as KROG 22-05. This trial was registered at ClinicalTrials.gov (NCT05440149) on June 30, 2022.

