### Sample size calculation

The PORT-N1 trial was designed to determine whether the omission of RNI from BCS and PMRT in patients undergoing a mastectomy reduced treatment efficacy. The expected 7-year DFS of the control group in this trial is 90%, based on a previous multicenter retrospective studies conducted by the KROG. The rate of recurrence at 7 years was 12% for the no-PMRT group in KROG 14-23 [20]; the recurrence rate is expected to be lower in the PORT-N1 trial because more than a decade has passed since the previous study. The KROG 14-18 study analyzed pN1 breast cancer patients who underwent anthracycline and taxane chemotherapy, and reported a 5-year DFS of 92.4%, with no difference seen between BCS plus PORT and mastectomy alone groups [21]. Another analysis of KROG 14-18 data compared WBI alone and WBI plus SCL irradiation, and obtained 5-year DFS rates of 94.4 and 92.6%, respectively [19]. The sample size calculation for the PORT-N1 trial assumes a non-inferiority margin of 5%, type I error rate of 5%, 4-year recruitment period, 7-year follow-up, and exponential distribution for time to progression; 134 DFS events are expected, and 525 patients are required for each group for a power of 80%. Assuming a dropout rate of 5%, the final number of patients to be randomized is 1106 (553 for each group).

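### The log-rank test named for the primary endpoint is not linked to the 5% non-inferiority margin, so the stated analysis does not match the non-inferiority objective or the sample size

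*Protocol article*

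**What the plan says.** The objective is given in the abstract: "PORT-N1 aims to demonstrate non-inferiority of the experimental group by comparing 7-year disease-free survival rates with the control group". The Study design section also calls the trial a non-inferiority trial. Under Endpoint and statistics, "The primary endpoint of this trial is 7-year DFS".

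The margin appears only under Sample size calculation. With a control 7-year DFS of 90%, the calculation "assumes a non-inferiority margin of 5%, type I error rate of 5%, 4-year recruitment period, 7-year follow-up". It arrives at 134 DFS events and 525 patients per group for 80% power, raised to 553 per group (1106 in total) for 5% dropout. Sidedness is not stated.

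The comparison itself is under Endpoint and statistics: "DFS, LRFS, DMFS, and OS rates will be calculated by Kaplan–Meier analysis and compared using the log-rank test". The threshold there is P < 0.05, again without sidedness. The Cox model is assigned to covariate effects. That section gives no margin, no confidence limit to be held against one, and no rule for concluding non-inferiority.

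**The concern.** One sentence assigns the same test to the primary endpoint and to three secondary endpoints that have no margin. The natural reading is therefore the usual log-rank test, whose null hypothesis is equal hazards. A non-inferiority question has a different null: that the experimental arm is worse by at least the margin. Rejecting equality, or failing to reject it, does not decide that question.

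The test also compares whole curves, while the endpoint is a rate at 7 years.

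The article's conclusion says that a non-inferiority result would support a smaller field after breast-conserving surgery or no radiotherapy after mastectomy. The rule that separates shown from not shown should therefore be fixed in the plan before results are seen.

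**Working it through.** **Inputs.** From Sample size calculation: control 7-year DFS 90%, margin 5%, type I error 5%, power 80%, exponential times, 134 events, 525 per group. From Study design: "This trial is anticipated to run for 11 years, with a 4-year recruitment phase and 7-year follow-up". Assumptions made here: the margin is absolute (90% against 85%), the arms are truly equal for power, accrual is uniform, and the log hazard ratio (HR) is approximately normal with standard error 2/√events.

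**1. Reproduce the plan's figures.**
- Margin as an HR: ln(0.85)/ln(0.90) = 1.5425, log 0.4334.
- Events, Schoenfeld, one-sided 5%: 4 × (1.645 + 0.842)² / 0.4334² = 132. Freedman gives 136. The stated 134 lies between them.
- Event probability with 4 years' accrual and 7 further years, hazard λ = −ln(0.90)/7 = 0.01505: 1 − (e^(−7λ) − e^(−11λ))/(4λ) = 0.1266.
- Patients per arm: 2 × (1.645 + 0.842)² / (0.1266 × 0.4334²) = 520 (stated 525). Expected events: 1050 × 0.1266 = 132.9 (stated 134).
- Dropout: 525/0.95 = 552.6, so 553 per arm and 1106 in total, as stated.
- One-sided 2.5% instead needs 168 (Schoenfeld) or 173 (Freedman) events, which does not match 134.

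The sample size is therefore that of a one-sided 5% test against the margin.

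**2. What each test requires with 134 events.** Standard error = 2/√134 = 0.1728.
- Margin test, one-sided 5%: observed HR at most exp(0.4334 − 1.645 × 0.1728) = 1.16.
- Two-sided test of equality: P < 0.05 only if the observed HR is above exp(1.96 × 0.1728) = 1.40 or below 1/1.40 = 0.71.

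An observed HR between 1.16 and 1.40 is non-significant on the log-rank test, yet non-inferiority is not shown.

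**3. If non-significance were taken as non-inferiority, with the truth at the margin.** The chance of passing is about Φ(1.96 − 0.4334 × √events/2).
- 134 events (the stated number): Φ(−0.55) = 29%.
- 525 × 0.10 + 525 × 0.15 = 131.25 events (each patient followed for 7 years): 30%. Simulation gave 31% to 32%.
- 165 events (follow-up to year 11; event probabilities 0.1266 and 0.1883, so 525 × 0.3149): 20%. Simulation gave 20% to 21%.

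The planned error is 5%.

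**4. If P < 0.05 in favour of the experimental arm were required.** With equal arms the chance is Φ(−1.96) = 2.5%, against the planned 80%.

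**5. A margin-based rule at the planned size.**
- HR scale, 134 events: power Φ(0.4334/0.1728 − 1.645) = 80.6% at one-sided 5%, and 70.8% at one-sided 2.5%.
- Difference in 7-year DFS, 525 per arm: standard error √(2 × 0.9 × 0.1/525) = 0.0185; power Φ(0.05/0.0185 − 1.645) = 85% at one-sided 5%, and 77% at one-sided 2.5%. In simulation the one-sided 5% rule had an error at the margin close to 5% (4.6% to 5.3%).

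**The case against.** The best reply is that this is a condensed article. The full protocol and the SAP are not shown, and a detailed decision rule is commonly left to them. The objective, margin, type I error and power are all stated. A log-rank-type test against a shifted null (HR of at least 1.54) is a recognised non-inferiority method, and the stated events fit that design.

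Part of this stands. The absence of a detailed rule would not be a finding by itself, and it cannot be said that the trial has no valid primary test. What remains is that the article does name a test for the primary endpoint. The text describes no shifted null, and it applies the same test to endpoints without a margin. If an unseen plan holds a margin rule, the published sentence still differs from it.

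A reader might infer three stronger things that the documents do not support:
- That the trial's type I error is 20% to 32%. This follows only if P ≥ 0.05 is read as non-inferiority, which the article never says.
- That the margin's scale is left open. The abstract compares 7-year rates, and the margin stands beside a 90% rate, so absolute percentage points are the natural reading. Converting to an HR for sizing is routine, and drift between the scales when the control rate differs is a general caveat, not an error in this text.
- That the sample size is wrong. It reproduces on its own inputs.

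**Conclusion.** The point holds as a mismatch between the named test and the stated objective. The analysis sentence, read plainly, tests equality, while the objective and the sample size call for a one-sided 5% test against a 5-point margin (HR 1.54 at a control rate of 90%).

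Its size can be given only conditionally. The article fixes no single error rate, because it fixes no rule: the two simplest ways of using the named test miss the planned 5% error or the planned 80% power by a wide margin. The figures rest on the 90% control rate, an absolute margin and exponential times. The spread from 20% to 32% reflects whether follow-up ends at 7 years per patient or runs to year 11.

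Sidedness belongs to the same correction. P < 0.05 read as two-sided does not match a one-sided 5% design.

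**What to change.** Under Endpoint and statistics, give the primary endpoint its own statement: non-inferiority is concluded if the upper limit of the one-sided 95% confidence interval for the difference in Kaplan–Meier 7-year DFS (control minus experimental) is below 5 percentage points.

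Under Sample size calculation, state that the 5% type I error is one-sided and the margin absolute. Report the Cox HR for treatment with its confidence interval as supportive, and keep the log-rank test for the secondary endpoints.

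An upper limit for the HR held against 1.54 would also be a valid rule. The difference is preferred here because it is on the scale of the stated endpoint.

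The cost is a wording change in the protocol and analysis plan, made before results are seen. At one-sided 5% no extra patients or data are needed. If the sponsor intends one-sided 2.5%, the planned size gives about 71% power on the HR scale and 77% on the difference scale, so the sample size would have to be revisited.

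### The two randomization strata are not carried into the stated treatment comparison; a stratum-weighted 7-year DFS difference would be a small, free improvement

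*Protocol article*

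**What the plan says.** Under Screening and randomization, the article fixes the method, "The stratified block randomization method will be used to prepare a randomization table", and the factors: "The stratification factors include surgery type (BCS vs. mastectomy) and histologic subtype", the latter being triple-negative against non-triple-negative. The abstract says the same.

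Under Endpoint and statistics it gives the comparison: DFS and the three secondary endpoints are estimated by the Kaplan-Meier method and "compared using the log-rank test". The next sentence adds a model: "The Cox proportional hazards model will be used to evaluate the impact of covariates on clinical endpoints". The covariates are not listed, and the model is not described as the treatment comparison. A significance threshold of 0.05 follows. Neither sentence mentions the randomization strata.

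Under Study design and Interventions and follow-up, surgery type sets the treatment contrast. After breast-conserving surgery it is whole-breast irradiation with or without regional nodal irradiation. After mastectomy it is radiotherapy or none.

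**The concern.** When randomization is balanced within strata, the usual practice is to use the same strata in the analysis. The estimate then benefits from the balance, and patients are compared with others who faced the same choice. That matters more than usual here, because surgery type is not only prognostic: it separates two different de-escalation questions. The Discussion also records a specific worry about locoregional recurrence when radiotherapy is omitted completely after mastectomy.

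The analysis section names a test, a model and a threshold, so its ordinary reading is a log-rank test of treatment without strata. What is at stake is a little precision in the primary 7-year DFS estimate, and an analytic choice left open in a trial where investigators know the allocation.

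**Working it through.** **1. The plan's own figures.** Inputs from Sample size calculation: control 7-year DFS 90%, margin 5 points, type I error 5%, power 80%, 4 years of recruitment, 7 years of follow-up, exponential times.

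- Margin as a hazard ratio: ln(0.85)/ln(0.90) = 1.5425, with log 0.4334.
- Events (Schoenfeld, one-sided 5%): 4 × (1.645 + 0.842)² / 0.4334² ≈ 132. The plan states 134. A two-sided 5% would need 168, so one-sided is the reading that reproduces the plan.
- Hazard: −ln(0.90)/7 = 0.01505 per year. Event probability with 4 years of uniform accrual and 7 years after the last entry: 0.1266. Patients per group: 132/(2 × 0.1266) ≈ 522 (plan: 525). Expected events: 1050 × 0.1266 = 132.9.
- Dropout: 525/0.95 = 552.6, so 553 per group and 1106 in all.

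The figures reproduce, and none of them depends on whether the analysis is stratified.

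**2. What weighting by stratum gains on the 7-year difference.** Assumptions, not in the protocol: 15% triple-negative, with a hazard h times that of the rest, and overall 7-year DFS of 90%. Solve 0.85·exp(−H) + 0.15·exp(−hH) = 0.90 for H. Then compare the average within-stratum binomial variance v with 0.90 × 0.10 = 0.09. Power is Φ(0.05/√(2v/525) − 1.645).

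| h | DFS, other / triple-negative | v | v/0.09 | Power |
|---|---|---|---|---|
| no strata | 90% | 0.0900 | 1 | 85.4% |
| 2 | 91.2% / 83.2% | 0.0892 | 0.991 | 85.7% |
| 3 | 92.1% / 78.1% | 0.0875 | 0.972 | 86.3% |

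The 85.4% baseline belongs to a binomial comparison with complete 7-year follow-up. It is not the plan's event-based 80%, and only the change down the column matters here. A simulation of 1050 patients in stratified blocks (15% triple-negative, 35% mastectomy, prognostic hazard ratios 1.5 to 3, all assumed) gave a similar gain for the stratum-weighted difference: about 0.4 to 0.9 points.

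**3. What stratifying the log-rank test gains.** In that same simulation, power was 80.3–81.1% without strata and 79.9–80.2% with them. A second simulation tested against the hazard-ratio margin, with 1050 patients, 4000 runs per scenario, and an assumed 12% triple-negative and 35% mastectomy:

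| Prognostic HR (triple-negative, mastectomy) | Power, unstratified / stratified | Type I error, unstratified / stratified |
|---|---|---|
| 1, 1 | 80.2% / 80.3% | 5.5% / 5.4% |
| 1.5, 1.2 | 79.4% / 79.3% | 5.1% / 5.1% |
| 2, 1.5 | 80.9% / 80.5% | 5.2% / 5.0% |
| 3, 1.5 | 79.6% / 78.7% | 4.4% / 4.1% |

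Monte Carlo standard errors are about 0.6 points for power and 0.35 for type I error. Stratifying the test gains no power and makes no meaningful difference to type I error.

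**4. Attenuation of the hazard ratio.** Under the assumptions of step 2, a within-stratum hazard ratio of 1.5425 corresponds to an overall 7-year cumulative-hazard ratio of 1.538 (h = 2) or 1.530 (h = 3). The shift is towards 1, but it is at most 0.0125.

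**5. Sparse strata.** With 15% triple-negative and 35% mastectomy, and the two taken as independent, the smallest of the four strata holds 0.15 × 0.35 × 1050 ≈ 55 patients, or about 28 per group. A rule for pooling may be needed.

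**The case against.** The strongest objection is that the article never says the test is unstratified. It is a condensed text, and whether a log-rank test is stratified, or which covariates enter a Cox model, is often left to a full protocol or analysis plan, which is not shown. Nothing in the article contradicts a stratified test, and the two factors are obvious candidates for the Cox model. This stands. A reader might infer that the plan ignores the factors, but the text does not support that. It supports only that the stated comparison does not carry them forward.

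A reader might also infer that the log-rank test loses precision, or that a hazard ratio pulled towards 1 favours non-inferiority. Neither holds in substance. The simulations show no power gain from stratifying the test and no inflation of type I error. The margin is itself a difference in overall 7-year DFS, and its hazard-ratio form of 1.5425 comes from overall survival of 90% and 85%. An overall hazard ratio therefore matches the margin, and its gap from the within-stratum ratio is non-collapsibility rather than bias.

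Finally, an ordinary log-rank test at P < 0.05 tests equality and not the margin. That is a separate matter. Stratifying would not cure it, and it lends no weight here.

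**Conclusion.** The point holds as a low-severity improvement. Randomization uses two factors, one of which defines the treatment contrast, and the stated treatment comparison does not mention them. A stratum-weighted 7-year DFS difference would gain under about 1 percentage point of power. That size rests on an assumed triple-negative share of 15%, prognostic hazard ratios of 1.5 to 3 and, in the simulation, a 35% mastectomy share. The protocol gives none of these.

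The 134 events, 525 per group and 1106 in all stay as they are. The better reasons to act are that each patient is compared within her own treatment contrast, and that an open-label trial is left with one fewer choice to make after the data are seen.

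**What to change.** State, before the data are analysed, that the primary estimate is the difference in Kaplan-Meier 7-year DFS, weighted by stratum size over the four randomization strata. Its confidence limit is to be compared with the 5% margin, at the one-sided 5% level that reproduces the sample size. Give a rule in advance for pooling sparse strata, for example across triple-negative status within surgery type, so that the treatment contrasts stay separate.

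Report the treatment hazard ratio from a Cox model stratified by the same two factors, as support for the primary estimate. Changing only the log-rank test to its stratified form would not deliver the gain.

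The cost is a sentence or two in the analysis section or the analysis plan. No new data, patients or follow-up are needed. If a fuller document already says this, a pointer to it is enough.
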